#### Primary endpoint

The primary endpoint is dyadic ACP communication (between adolescent and parent) at 3 months (T1), using the Parent-Adolescent Communication Scale (PACS) [38], a validated questionnaire to measure the adolescent’s perception of their communication, as applied to pACP themes with (both of) the parent(s). The Parent-Adolescent Communication Scale [38] entails two subscales: 1) openness in communication subscale; 2) problems in communication subscale, including 20 items, that can be rated from 1 to 5 and produce factor-derived scores (range: 10–50). Items are summed for each scale, so that higher scores indicate more openness and more problems. The scores for items on the Problems subscale are reversed in value. The score ranges from 20 to 100 on the full scale. Both subscales have demonstrated strong internal consistency (alpha = 0.87–0.78) and test-retest reliability (r = 0.78–0.77) [37]. The questionnaire was translated to Dutch following a forward-backward translation procedure, in collaboration with an independent translation agency. The adolescent will fill out the PACS about both parents, if applicable.

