#### Secondary endpoints

One of the secondary endpoints is dyadic communication (between adolescent and parent(s) at 7 months (T2). The other secondary endpoints will be measured at baseline (T0), T1 and T2 and include:
adolescent’s/parents’ attitudes to talking about ACP themes with his/her parent(s)/child (self-developed items)adolescent’s/parents’ self-efficacy towards talking about ACP themes with his/her parent(s)/child (self-developed items)parents’ self-efficacy towards talking with their child and letting their child talk in different situations (self-developed items)adolescent’s/parents’ behaviour of talking about ACP themes with his/her parent(s)/child (self-developed items)adolescent’s/parents’ intention to talk about ACP themes with his/her parent(s)/child (self-developed items)adolescent’s behaviour of talking about ACP themes with his/her paediatric oncologist (self-developed items)adolescent’s intention to talk about ACP themes with his/her paediatric oncologist (self-developed items)adolescent’s quality of life (EQ-5D-Y [34])parents’ perception of shared decision making in the last clinical encounter (CollaboRATE Scale [33, 36])adolescent’s/parents’ level of anxiety in the past week (PROMIS Anxiety [34, 39])paediatric oncologists’ behaviour of talking about ACP themes with the family (self-developed items)paediatric oncologists’ intention to talk about ACP themes with the family (self-developed items).

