### Data collection procedures

Quantitative data is collected at baseline (T0), after 3 months (T1), and after 7 months (T2) (see Fig. 3), using self-reported questionnaires that are pseudonymized using individual identifier codes attributed by the data collector. During a home visit, the data collector will gather written consent from both parents and written assent from the adolescent, immediately after which the baseline questionnaire is provided to the participant (paper-pencil or online using ‘LimeSurvey’, depending on the choice of the participant). The data collector will fill out the questionnaire together with the adolescent in an interview format. This will be done in a separate room from the parent(s), to avoid that the adolescent is being influenced by their presence. Parent(s) can either choose to fill out their questionnaire independently at the same time or later. The paediatric oncologist mentioned by the family as the one with whom they have most contact about care and treatment will receive a baseline questionnaire about the adolescent via an e-mail link. The data collector will send out one reminder to the parents and paediatric oncologist after 1 week. Data collection procedures are repeated at T1. At T2, questionnaires are sent to parents and adolescents, either online or via postal mail. To reduce loss to follow-up, improve retention, and encourage adolescents to fill out the questionnaires, retention gifts will be provided after completion of each data collection, at T0, T1 and T2.

Data collection procedures for the process evaluation (Additional file 2), include:
structured diary filled out by facilitators: the facilitators keep track of all activities they perform regarding the BOOST pACP program by filling out a structured diary, including multiple choice and open-ended questions, after each BOOST pACP conversation session. The diary will be completed in a Word template and will be stored in a secure folder.semi-structured individual interviews with facilitators; both facilitators will be interviewed for 60 min by a researcher at 6 months, 12 months, 18 months and after the end of the data collection period at 24 months.semi-structured individual interviews with a variety of involved paediatric oncology teams after 12 months and after study completion, at 24 months.each BOOST pACP conversation is recorded by audio (after informed consent of participants).

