### Data analysis

The intervention and control group will be described using descriptive summary statistics (mean, standard deviation, count percentage). We will test for significant differences in the primary and secondary endpoints, between the intervention and control group at baseline and at T1 (3 months from T0), and T2 (7 months from T0) while adjusting for baselines scores.

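### At T2 the adolescent questionnaire is sent out without the privacy safeguard used at T0 and T1, so T1-to-T2 change in arm means is mixed with a change of mode

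*Protocol article*

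**What the plan says.** All the relevant text on mode is in one paragraph of the protocol article, under Data collection procedures.

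- **T0.** "The data collector will fill out the questionnaire together with the adolescent in an interview format". The reason for privacy follows: "This will be done in a separate room from the parent(s), to avoid that the adolescent is being influenced by their presence".
- **T1.** "Data collection procedures are repeated at T1".
- **T2.** "At T2, questionnaires are sent to parents and adolescents, either online or via postal mail". The paragraph mentions no interview, separate room or other privacy arrangement for this visit.

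The Primary endpoint section places the PACS primary endpoint at T1 and describes the instrument as the adolescent's own perception of communication with the parents: "The adolescent will fill out the PACS about both parents, if applicable". The Secondary endpoints section and Table 3 make the PACS at 7 months a secondary endpoint. Table 3 also schedules the adolescent's attitude, self-efficacy, behaviour, intention, anxiety and quality-of-life measures at T2. The Data analysis section plans comparisons between arms at T1 and at T2, "while adjusting for baselines scores".

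**The concern.** The protocol article judges that a parent's presence could influence what the adolescent reports, and it guards against this at two of three visits. The reason applies equally at the third, where the same scale asks respondents aged 10 to 18 about the same parents. A form that arrives by post or link may be completed with a parent nearby or helping.

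T2 is also the only measurement after the three-month programme, so readers will look to it for evidence that any effect lasts. Every adolescent changes mode at the same step as the time point. A rise or fall in an arm's mean from T1 to T2 therefore has two possible explanations that the data cannot separate. In addition, families know their allocation, and only intervention parents have taken part in sessions about talking with their child. Parental influence on the T2 answers might therefore differ between arms.

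**Working it through.** **1. The plan's own figure.** Inputs from the Sample size section: difference 7 at T1, SD 11.4, alpha 0.05 (taken as two-sided), power 80%, retention 90%.

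- Normal approximation: n = 2 × (1.96 + 0.842)² × 11.4² / 7² = 41.6, so 42 per arm. The two-sample t-test gives 42.6, so 43 per arm, as stated.
- Enrolment: 2 × 43 = 86, and 86 / 0.90 = 95.6, so 96, as stated.

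This calculation is for T1 and is not in dispute.

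**2. What a mode change does to each quantity.** Suppose the true arm difference is d at both visits and there is no true change over time. Let the T2 mode add c points in both arms and a further b points in the intervention arm only.

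| Quantity | Value |
|---|---|
| T1 arm contrast | d |
| T2 arm contrast | (d + c + b) − c = d + b |
| T1-to-T2 change, intervention mean | c + b |
| T1-to-T2 change, control mean | c |

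The common shift c cancels from the T2 contrast but stays in both within-arm changes. Only b reaches the contrast.

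**3. Illustration.** The documents give no value for c or b, so those used here are assumptions. I take d = 7, SD 11.4 and 43 per arm at T2 (a further assumption, since the retention figure accompanies the T1 calculation). The standard error is 11.4 × √(2/43) = 2.46, and power is for an unadjusted two-sided test.

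| c | b | T2 contrast | Change, intervention | Change, control | Power at T2 |
|---|---|---|---|---|---|
| 0 | 0 | 7 | 0 | 0 | 0.81 |
| −3 | 0 | 7 | −3 | −3 | 0.81 |
| 0 | −2 | 5 | −2 | 0 | 0.53 |
| −3 | −3.5 | 3.5 | −6.5 | −3 | 0.30 |

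Row 2 shows apparent decay in both arms with an intact contrast. Rows 3 and 4 show a lasting effect that looks as if it were fading. With b = +2 the contrast would be 9, an overstatement of 2/7 = 29%.

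**4. Precision.** A baseline taken in another mode might correlate less well with T2. If the correlation fell from an assumed 0.7 to an assumed 0.5, the standard error would rise by √(0.75/0.51) = 1.21. At 0.5 the residual SD is 11.4 × √0.75 = 9.9, and power for a difference of 7 with 43 per arm is 0.91. That is above the planned 0.80, because the sample size took no credit for baseline adjustment.

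**The case against.** The strongest reply is that the analysis actually planned is protected. The Data analysis section specifies baseline-adjusted comparisons between arms at each visit, and no test of change from T1 to T2 is named. Both arms switch mode together, so a common shift cancels. This stands, and it limits the point to how T1 and T2 are read side by side and to a possible differential effect.

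Second, the T2 mode may not be the worse one. Under Allocation, the data collector tells families their arm, and the same role conducts the T1 interview. Self-completion removes any influence from an interviewer who knows the allocation. This also stands: the documents do not show which visit is more prone to bias. It does not make the two visits comparable, because each would be open to a different influence.

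Third, the article condenses a fuller protocol, and an instruction to complete the form alone may exist there. Unsupervised completion at home is an inference from the sending route, not something the article states. That is fair. If the instruction exists, what remains is to record compliance and word the interpretation accordingly.

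A reader might go further and infer that intervention parents will push T2 answers in the programme's favour. Nothing in the documents shows that they would influence answers more than control parents, or in which direction.

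**Conclusion.** The point holds as a modest one about secondary endpoints. The article gives a reason for a privacy safeguard, applies it at T0 and T1, and states no equivalent at T2, where the reason is unchanged. As a result, T1-to-T2 change in arm means is confounded with mode, and the T2 contrast is exposed to bias if parental influence differs between the unblinded arms. The size and direction of such bias are unknown, and the point values above only illustrate the mechanism.

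Three stronger readings are tempting but unsupported:

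- **The randomised T2 effect is itself confounded with mode.** It is not, because both arms change mode together. Bias needs a shift that differs by arm.
- **The primary result is affected.** It is not. The T1 PACS and its baseline are collected by the same procedure.
- **The trial loses needed precision at T2.** The fall in correlation is assumed, a longer interval could cause it without any mode effect, and the assumed lower value still leaves power above plan.

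**What to change.** At T2:

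1. Send the adolescent's questionnaire separately from the parents' form, by its own link or with its own sealed return envelope.
2. Instruct the adolescent to complete it alone.
3. Add one item asking whether a parent was present or helped.
4. Report a T2 sensitivity analysis by that item.
5. State that T1-to-T2 differences will not be read as persistence or decay without noting the change of mode.

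The cost is one added item, a revised mailing and a small extra analysis. The presence item is measured after randomisation, so the analysis by it is descriptive and cannot correct the T2 contrast.

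A private remote call at T2 would restore the T1 mode more closely but is optional. It uses data-collector time and would bring back an interviewer who knows the allocation. The primary endpoint and sample size do not change.

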### Data management

All questionnaires will contain a pseudonymizing code consisting of a unique number that is linked to the participant’s name***.*** Data collectors will keep a record of these codes in a secured folder that is not accessible to the researchers. The data collector is responsible for noting the correct unique number of the paper version of the questionnaires at T0, T1 and T2 or for forwarding the code in the email to participants. For the questionnaires of the paediatric oncologists, the data collector will communicate the name of the adolescent with the corresponding code. The paediatric oncologist will be asked to note down the adolescent’s code in the online questionnaire. Data collectors will keep an excel file to indicate to what codes they have sent the questionnaires and share this with researchers. Using this file, the researchers will keep track of responses and will use the unique code to communicate with the data collector to whom a reminder may need to be sent out. Data from paper-and-pencil questionnaires are entered as soon as possible after receipt. Online questionnaires will be automatically saved in a secure open-source web-based survey application (LimeSurvey). Written informed consent files and paper questionnaires are stored in a lockable filing cabinet in a room with restricted access on campus. The file with the participants’ names, address and other identifiable information will be stored in one file. This file will be restricted to the data collectors and ACP facilitators only.

#### Confidentiality

The collected and transferred data will be pseudonymized to ensure that participants’ privacy and personal information are protected. In transcriptions of the interviews, all information that can contribute to tracing and identifying the participants will be removed or replaced. We will use sufficient safety measures to protect the data, including a virtual server firewall, back-up systems and sufficient access controls (i.e., ID and ultrahigh password regulator and frequent password changes).

#### Dissemination

The results of this study will be submitted for publication in peer-reviewed journals and will be presented to the paediatric wards of the participating hospitals and at national and international research and professional conferences. Furthermore, we will disseminate via the website, social media and newsletter of the research group (endoflifecare.be).

### Data analysis

The intervention and control group will be described using descriptive summary statistics (mean, standard deviation, count percentage). We will test for significant differences in the primary and secondary endpoints, between the intervention and control group at baseline and at T1 (3 months from T0), and T2 (7 months from T0) while adjusting for baselines scores.

#### Primary hypothesis testing

The hypotheses related to the primary endpoint, parent-adolescent communication (PACS), will be analysed using a mixed model with the T1 measurement value for parent-adolescent communication as outcome variable and randomization group and baseline measure of parent-adolescent communication as predictor variables. Random effects that we will include in our mixed model are hospital and line of treatment. We will perform analyses on both intention-to-treat and per-protocol principles, with the intention-to-treat as the primary approach. In the intention-to-treat analysis, all participants who were enrolled and randomised will be accounted for in the main analysis, regardless of whether they completed the BOOST pACP program or not. The linear mixed models we intend to apply handle missing data through maximum likelihood estimation (i.e. assuming data is missing at random), so no missing data imputation should be applied. In case we do decide to apply multiple imputation, predictors for the imputation model will include the baseline measurement, randomization group, age and other possibly confounding variables (e.g. prognosis). In the per-protocol analysis, we will focus on families of which at least one parent was involved in all BOOST pACP conversations. During this analysis, we regard the family as a cluster because it is possible that during some conversation sessions both parents are present, while during others only one parent is present. Therefore, we will add the presence of parents during the conversation sessions as time-varying covariates.

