### Sample size

We consider demonstration of an intervention effect on the primary endpoint as a success. The primary endpoint is the score for the Parent-Adolescent Communication Scale (PACS) [38] at 3 months (T1).

To detect a minimal relevant difference between intervention and control group at T1 of 7 with a pooled standard deviation in both groups of 11.4, with alpha at 0.05 and 80% power (1-β = 0.80), a sample of *n* = 43 is needed in each arm. Based on the experiences with the FACE intervention [40], we anticipate a 90% retention rate, similar to the FACE intervention, resulting in an estimation of 96 families in total to be enrolled.

Two other studies found a smaller difference in PACS scores between the intervention and control group (e.g. 2.57 [41] and 2.21 [42]). However, both of these intervention studies entailed minimal in-person contact and sending prompts to the parents by mobile phone. The components of the BOOST pACP program entail intensive in-person contact moments, specifically targeted at behavioural constructs to improve parent-adolescent communication on ACP themes. Therefore, we expect to see a larger effect on the PACS scale, compared with the interventions described above.

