### Allocation

Randomization will be performed after at least one of the parents has completed the baseline measurement. Block randomization with a 1:1 allocation ratio to either the intervention arm or the control arm will be performed, using a concealed envelope method. To ensure equal allocation of subgroups, we will stratify the allocation by age (10–14 years old vs 15–18 years old). We have opted for these age strata, because the cognitive development of adolescents between 10 and 14 years differs from those between 15 and 18 years [43, 44] which might influence the way they are able to talk about their care and treatment.Allocation concealment will be ensured, as the randomization service will not release the randomization code until the adolescent has been recruited into the trial, which takes place after all baseline measurements have been completed. After randomization, the data collector will then inform the families of their allocation to one of the study arms.

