#### Secondary hypotheses testing

All secondary endpoints will be evaluated by testing the BOOST pACP program against the control group for each participant population separately (adolescents, parents and paediatric oncologists) with random effects being hospital and line of treatment.

For each of the primary and secondary endpoints, subgroup analyses will be performed using formal interaction tests to explore the extent to which the outcomes of the trial differ by gender, working situation and family situation of the parent(s) and gender and prognosis of the adolescent. Interaction terms between gender, working situation and family situation of the parent(s) and gender and prognosis of the adolescent on the one hand and the trial arms on the other hand will be added to the analysis models.

By including the baseline measurement as a predictor variable pre-existing differences will be controlled, enhancing the sensitivity of the analyses. Alpha is set at 0.05. To interpret the magnitude of the effects for the different outcomes, we will estimate effect sizes (Cohen’s d). Analyses will be conducted in IBM SPSS and R.

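### Randomisation is stratified by age, but the age stratum is in none of the outcome models that the protocol writes out

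*Protocol article*

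**What the plan says.** - **Allocation:** "To ensure equal allocation of subgroups, we will stratify the allocation by age", with two strata, 10–14 and 15–18 years. The reason given is that cognitive development differs between these groups and may affect how they can talk about care and treatment. No other stratification factor is named.
- **Primary hypothesis testing:** the outcome is the PACS score at 3 months, with "randomization group and baseline measure of parent-adolescent communication as predictor variables". The same section adds: "Random effects that we will include in our mixed model are hospital and line of treatment". Age is mentioned there once, as a predictor in a multiple-imputation model to be used only if the team decides to impute.
- **Secondary hypotheses testing:** the same two random effects are used, with the baseline measurement as a predictor. Subgroup interactions examine whether outcomes "differ by gender, working situation and family situation of the parent(s) and gender and prognosis of the adolescent". Age is not on that list.
- **Sample size:** the target is a 7-point difference in PACS at 3 months. The SD is taken as 11.4, and the calculation is made "with alpha at 0.05 and 80% power", giving 43 per arm. Allowing for 90% retention, 96 families are to be enrolled.

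**The concern.** Stratified blocks force the arms to be nearly balanced on age, so the treatment estimate varies less from trial to trial than under simple randomisation. A model without the stratum does not see this. Whatever variance age explains beyond the baseline score stays in the residual, so the reported standard error is larger than the true one. Intervals are then too wide and the test rejects less often than its nominal level.

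The protocol's own reason for stratifying is that age may bear on communication, and the primary endpoint is the adolescent's own rating of communication. The design thus treats age as potentially prognostic and the analysis does not. Some precision is at stake; validity is not.

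**Working it through.** **1. The plan's own figure.** With a difference of 7, an SD of 11.4, two-sided alpha of 0.05 and 80% power:

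n per arm = 2 × (1.96 + 0.8416)² × (11.4/7)² = 2 × 7.849 × 2.652 = 41.6, so 42 by the normal approximation. The t-based calculation gives 43 (power 0.804). Then 86/0.90 = 95.6, so 96 families. The stated figures reproduce. The article does not state sidedness, but a one-sided test would need only 33 per arm, so two-sided fits.

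**2. Inputs for the check.** From the article: SD 11.4, 86 analysable families, 1:1 blocks within two age strata, and a model with arm and baseline PACS. Assumed, because the article gives no figures: correlation of 0.5 between baseline and 3-month PACS; equal-sized age strata; block size 4; an age-group difference of 0, 2, 4 or 6 PACS points, independent of baseline. Hospital and line of treatment are left out so that the effect of age stands alone.

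**3. Formulas.** Residual variance after baseline is 11.4² × (1 − 0.5²) = 97.47. The share explained by an age gap g with equal strata is R² = 0.25g²/97.47. Omitting age inflates the standard error by 1/√(1 − R²). Type I error becomes 2 × [1 − Φ(1.96/√(1 − R²))].

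| Age gap | R² | SE inflation | Type I error by formula |
|---|---|---|---|
| 0 | 0 | 0% | 0.050 |
| 2 | 0.010 | 0.5% | 0.049 |
| 4 | 0.041 | 2.1% | 0.045 |
| 6 | 0.092 | 5.0% | 0.040 |

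**4. Simulation**, 6,000 trials per setting, each analysed by ANCOVA without and then with the age stratum (shown as without → with). The SE column is from the runs with no treatment effect.

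| Age gap | SE of arm effect | Type I error | Power at 7 | Power at 5 |
|---|---|---|---|---|
| 0 | 2.133 → 2.134 | 0.053 → 0.054 | 0.898 → 0.897 | 0.634 → 0.635 |
| 2 | 2.138 → 2.127 | 0.051 → 0.053 | 0.891 → 0.893 | 0.637 → 0.642 |
| 4 | 2.136 → 2.092 | 0.046 → 0.050 | 0.899 → 0.907 | 0.633 → 0.647 |
| 6 | 2.133 → 2.032 | 0.040 → 0.051 | 0.910 → 0.926 | 0.646 → 0.681 |

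The standard error of a simulated 5% rate is √(0.05 × 0.95/6000) = 0.003, so 0.051 to 0.054 cannot be told from nominal. Formula and simulation agree.

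**The case against.** **The effect is small and errs on the safe side.** This stands. Omitting the stratum does not bias the estimate, and any error lowers the type I rate. Baseline PACS is already in the model, so only what age explains beyond it counts. An age gap of 6 points is close to the trial's minimal relevant difference of 7, so the upper end of the range is generous.

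**An article may leave model detail to the analysis plan.** This applies less here, because the article writes out the outcome, the predictors, the random effects and the interaction terms. The point concerns the model as stated.

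**Stronger readings that the documents do not support:**

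- *Power would rise from 80.4% to 82–84%.* The 80.4% belongs to an unadjusted t-test, whereas the planned model adjusts for baseline. Those gains also need age to explain 5–10% of the total variance, that is, gaps of 2 × 11.4 × √0.05 = 5.1 to 2 × 11.4 × √0.10 = 7.2 points. No figure in the article supports gaps of that size.
- *Hospital and line of treatment must become fixed effects because they have few levels.* With four hospitals, 86 families and an assumed intraclass correlation of 0.02–0.05, the hospital variance is indeed estimated at zero in about 45–61% of trials under maximum likelihood. But randomisation is not stratified by hospital, and a zero estimate simply leaves a valid ANCOVA. In a small simulation (600 runs per cell, correlation 0.05), the arm standard error was 2.09–2.10 with random hospital and 2.11–2.13 with fixed or no hospital; power at 7 points was about 0.90 in all three. No bias or loss of precision is shown. The article does not give the number of line-of-treatment categories.
- *Age is an effect modifier that the protocol argues for but never tests.* The Allocation section gives a prognostic reason for balancing the arms. It does not say that the programme's effect should differ by age.
- *Age appears in no model at all.* It is in the contingent imputation model. The accurate statement is that no outcome model contains it.

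**Conclusion.** The point holds as a minor mismatch between design and analysis: the only stated stratification factor is absent from every outcome model specified. If age predicts PACS beyond baseline, the standard error is about 0.5–5% too large and type I error lies between about 0.051 and 0.040. The power lost is about 0–2 points at a true difference of 7 and up to about 3.5 points at 5. These figures rest on the assumed age gaps of 2–6 points, the assumed correlation of 0.5, equal strata and blocks of four. If age adds nothing beyond baseline, the cost is nil. Neither the validity of the trial nor the planned 96 families is in question.

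**What to change.** Add the age stratum (10–14 versus 15–18, as used at randomisation) as a fixed effect in the primary model and in the secondary outcome models. Record the change before the analysts see outcomes by arm, so that it cannot look data-driven. It costs one sentence of wording and one degree of freedom. No new data are needed, because the stratum is known for every randomised family, and the sample size does not change. Nothing in this point requires changing the random effects or the subgroup list.

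### The primary model has one T1 score per adolescent, so maximum likelihood gives a complete-case analysis and does not justify ruling out imputation

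*Protocol article*

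**What the plan says.** All of the following is in the protocol article, Primary hypothesis testing.

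- **Outcome and predictors.** The primary analysis is a "mixed model with the T1 measurement value for parent-adolescent communication as outcome variable", with randomisation group and baseline PACS as predictors.
- **Random effects.** "Random effects that we will include in our mixed model are hospital and line of treatment". There is no participant effect and no repeated visit.
- **Missing data.** "The linear mixed models we intend to apply handle missing data through maximum likelihood estimation", under an assumption of missing at random, from which the text concludes that missing values should not be imputed.
- **Fallback.** The next sentence keeps imputation open: "In case we do decide to apply multiple imputation, predictors for the imputation model will include the baseline measurement, randomization group, age", plus other possible confounders, with prognosis as the example. No condition for using it is given, and T2 PACS is not among the named predictors.

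Table 3 and the Secondary endpoints section show that PACS is also collected from the adolescent at baseline (T0) and at 7 months (T2). T2 PACS is a secondary endpoint and does not enter the primary model.

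**The concern.** Likelihood methods use an incomplete case through that person's other outcome measurements. A repeated-measures model has such measurements; the model described here does not. The reason given for not imputing therefore belongs to a different model.

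Two things follow. First, the missing-at-random condition behind the primary estimate is narrower than the text suggests. It conditions on arm, baseline PACS, hospital and line of treatment. It uses neither T2 PACS nor age and prognosis, although the protocol itself names the last two as imputation predictors. Second, the choice between no imputation and imputation is left open, so the primary analysis is not fully fixed.

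The protocol gives reasons to expect loss that is not purely random. The Harms section says participation may be emotionally stressful and describes facilitators discussing whether a family continues; facilitators are in contact only with the intervention arm. The section on discontinuing interventions excuses bereaved participants from follow-up questionnaires.

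**Working it through.** **1. The plan's own figures.** Inputs from Sample size: difference 7, SD 11.4, alpha 0.05 (taken as two-sided), power 80%, retention 90%.

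- Per arm, normal approximation: 2 × (1.960 + 0.842)² × 11.4² / 7² = 2 × 7.85 × 129.96 / 49 = 41.6, so 42. The t-test version gives 42.6, so 43. The stated 43 reproduces.
- Total: 2 × 43 / 0.90 = 95.6, so 96. This also reproduces.
- Expected without T1: 96 × 0.10 = 9.6, leaving about 86.
- Power at 43 per arm is 80.4% (t-test) to 81.3% (normal). With all 48 per arm it would be 84.5% to 85.3%. The planned 80% is met after the loss.

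**2. What the likelihood does with a missing T1.** The stated model for adolescent i is

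T1ᵢ = β₀ + β₁·armᵢ + β₂·T0ᵢ + hospital effect + line-of-treatment effect + eᵢ.

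The observed-data likelihood is the joint normal density of all T1 scores with the missing ones integrated out. Integrating T1ᵢ out of a multivariate normal density removes row i and leaves the density of the remaining rows unchanged. The shared hospital and line effects do not alter this. The maximum likelihood estimate of β₁ is therefore the complete-case estimate.

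If T0, T1 and T2 were all outcomes, integrating out T1ᵢ would leave the density of (T0ᵢ, T2ᵢ). Through the within-adolescent covariance, that density carries information on the T1 means.

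**3. Numerical confirmation.** The stated model was fitted by maximum likelihood to 10 simulated trials of 96 with 10 T1 scores missing (assumed: baseline–T1 correlation 0.6, four hospitals, three lines of treatment). Every fit used 86 rows, and the treatment estimate differed from the complete-case fit by 0.

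**4. When this matters.** 4,000 trials of 96 were simulated with true effect 7, SD 11.4 and correlation 0.6, analysed by ANCOVA on arm and baseline. The missingness patterns are assumptions, not taken from the protocol.

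| T1 missingness depends on | Mean estimate (truth 7) |
|---|---|
| arm and baseline PACS only | 7.02 |
| T1 itself in the intervention arm (about 11% missing overall) | 8.0 |

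The first row shows the complete-case fit is sound under its own condition. The second is missing not at random, and a longitudinal model would not fully repair it either.

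**5. What a longitudinal model can recover.** With a common baseline mean μ₀, the T1 mean in an arm is β₀ + β₁·arm + β₂·μ₀, so the T1 arm contrast is β₁. If everyone who lacks T1 also lacks T2, the regression of T1 on T0 and arm is still estimated from T1 completers alone. Leaving the hospital and line effects aside, β₁ is then the same as in the stated model. The gain comes only from adolescents who miss T1 but return T2.

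**The case against.** Several points on the other side stand.

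- **The missing-at-random assumption is not false in itself.** The complete-case fit is valid under the narrower condition above, as the 7.02 shows.
- **Loss is planned for.** A reader might infer a power shortfall from the 10 families who drop out of the analysis. The documents do not support that: 96 was obtained by inflating 86.
- **The intention-to-treat promise.** The text says that "all participants who were enrolled and randomised will be accounted for in the main analysis", and a reader might take the model to break it outright. The same sentence ties the promise to whether families completed the programme. A family that stops the sessions but gives T1 is analysed as randomised. The sentence is loose about missing outcomes but is not plainly contradicted.
- **A quantified bias.** A reader might infer that the primary estimate will be inflated by a known amount and that using T2 would put it right. Nothing in the protocol gives the missingness mechanism. The repair also needs T2 from adolescents who missed T1, which withdrawn or bereaved families will generally not supply. T1 is collected by interview with the data collector, while T2 is sent online or by post, so T1 missing with T2 present may be the less common pattern.
- **Missing baseline PACS.** This would also remove an adolescent, but it is largely hypothetical. T0 is completed by interview directly after consent, and Allocation says the code is released after all baseline measurements, although it also allows randomisation after one parent's baseline.
- **Imputation is mentioned.** Predictors are named, and under Masking the analysts do not receive allocation, which lowers the risk of choosing imputation to suit the result. Further detail could properly sit in an analysis plan.

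None of this rescues the inference from maximum likelihood to no imputation. Completing the PACS about both parents (Primary endpoint) does not help either: an adolescent who misses T1 has neither score.

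**Conclusion.** The concern holds as a fault in a stated rule, not as an omission. For the model written down, maximum likelihood does no more than delete adolescents without T1, so it gives no reason to dispense with imputation. At the protocol's own retention this affects about 10 of 96 families. The estimate is unbiased only if missing T1 depends on nothing beyond arm, baseline PACS, hospital and line of treatment. Whether that fails, and by how much, cannot be derived from the documents; the 7.02 and 8.0 above rest on assumed mechanisms and only show that the answer depends on them. Planned power is not in question. The open option of imputation should be closed before outcome data are seen.

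**What to change.** Choose one of the following and state it as the primary analysis.

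1. **Joint model.** Fit PACS at T0, T1 and T2 together, with a common baseline mean, visit-by-arm terms and unstructured within-adolescent covariance. Keep the planned hospital and line-of-treatment effects, and take the T1 arm contrast as primary.
2. **T1 model with fixed imputation.** Keep the present model and pre-specify multiple imputation including T2 PACS, arm, baseline PACS, age stratum and prognosis.

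In either case, delete the statement that maximum likelihood makes imputation unnecessary and the open clause "In case we do decide to apply multiple imputation". Add a missing-not-at-random sensitivity analysis, for example delta-adjusted imputation, because families who leave altogether are not recovered by either option.

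The cost is wording and a few more covariance parameters. PACS is already collected at all three visits, so no new data are needed. The benefit is limited: outcome information is recovered only for adolescents who miss T1 but return T2.
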